### Patient and public involvement

This study will not involve patients. The study will constitute secondary analyses of UK survey data. The dissemination of the results will include communication channels and public engagement events that will involve youths and parents.

### Beneficiaries and target audiences

The project will be of interest to a range of academic and non-academic audiences. Research on tobacco control has a broad audience including epidemiologists, public health, policy researchers, governmental organisations and the UK general public. The findings of this research will be of benefit to the governments of UK countries as they will provide information on important impacts of an existing policy. This information will be of use if the policy is ever considered for repeal or modification. The evidence on the mechanisms of impact on young people’s smoking transition via their parents that will be generated from this project will be particularly valuable when considering extensions to smoke-free policies (eg, to more private spheres such as cars and homes or to other public spaces such as outdoor parks) or other tobacco control policies which may have impacts on youth via parental smoking.

Another group who may benefit from this study are policy-makers in other countries. Findings will be of international relevance as many countries are yet to implement partial or complete smoke-free public places legislation.^56^ The understanding of impacts and mechanisms gained from this study will help international policy-makers evaluate whether similar effects could be gained by implementing smoke-free or other policies within their own countries.

### Limitations

The causal interpretation of any impact on youth smoking uptake or parental smoking that we observe to be associated with the implementation of the smoke-free legislation rests on the assumption that this is the only relevant difference occurring at that point in time. Nevertheless, we will adjust for effects of some other relevant differences that could bias the results such as changes in tobacco taxation and the increasing availability of e-cigarettes, to see if we can differentiate the effects of the smoke-free legislation. The change in the legal age for purchase of cigarettes from age 16 to 18 years in 2007 for England, Wales and Scotland, and 2008 for Northern Ireland is particularly problematic, as it coincides so closely with the timing of the implementation of the smoke-free legislation (only differing by a year in Scotland and Northern Ireland, and being concurrent in England and Wales), so it may be difficult to statistically distinguish their effects. At worst this means that findings could be interpreted in terms of the package of policies implemented at that point (ie, the smoke-free legislation and the change in legal age), but our investigation of mechanisms of impact via parental smoking remains relevant in this regard. If some of the impacts can be attributed to parental smoking, this will further strengthen the case for a causal effect of the smoke-free legislation, as the change in legal age could be expected to have much less of an impact on adult smokers.

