Randomised controlled trials, often seen as the gold standard for establishing causality, are ethically and practically problematic in the context of studying population-level policies such as the smoke-free legislation. However, implementation of smoke-free public places legislation in the UK, which occurred in 2006 in Scotland and 2007 in the rest of the UK, provides the opportunity for a natural experimental approach^41^ to studying the impact of this policy on youth uptake, and the mechanisms by which these impacts occur. A natural experimental approach requires weaker assumptions for observed effects to be interpreted as causal than in most observational epidemiological studies. Specifically, if we were to observe that both parental smoking and the implementation of smoke-free legislation were associated with youth smoking uptake (thinking of parental smoking generally rather than in the context of this policy change), then causal interpretations of these associations both require an assumption of no (unmeasured) confounding. However, this assumption is considerably stronger for parental smoking (ie, that no other factor is causing both parental smoking and youth smoking) than for the timing of the legislation (ie, that no other factor causing/coinciding with the implementation of the legislation implementation also causes changes in youth smoking uptake).

Nevertheless, even for the implementation of smoke-free legislation, the assumption of no confounding may be problematic as the policy has not been the only important change happening in the UK that might impact on youth smoking uptake. Though acknowledged as one of the most significant changes in policy, smoke-free legislation was implemented in the UK within a period of incrementally increasing tobacco control.^42^ For example, sales taxes applied to cigarettes are subject to ongoing change, and the implementation of smoke-free legislation also coincided closely with a 2007 change in the legal age for purchase of cigarettes from 16 to 18 years. Another factor is the availability and use of e-cigarettes which has been growing in the UK since 2011.^43^ To attribute changes in youth smoking to the smoke-free policies, we will need to differentiate the impacts of the policy from these other contextual changes.

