A multilevel logistic regression model (with person-years nested within persons) will be used to investigate whether there is a step change or change in trend for the prevalence of parental smoking (any current smoking by either parent) after smoke-free public places legislations were implemented in the UK (Q3A) and whether observed changes (if any) differ by socioeconomic position (Q3B). This model will include all years of data for all respondents without any right or left censoring and will be adjusted for the young person’s age, gender, the overall temporal trend in parental smoking and overall differences between UK countries. The second stage of the modelling will additionally include parental education and interactions between parental education and the variables representing the implementation of the legislation.

Next, building on the models developed to assess whether the impact of the legislation on youth smoking transitions varied by socioeconomic position (Q2), parental smoking will also be included and we will assess whether this explains any observed differences associated with the implementation of the legislation (Q4A). We will test for interactions between parental smoking and the variables representing the implementation of the legislation to see if the influence of parental smoking changes after the legislation (Q4B) and then for a three-way interaction between parental smoking, legislation implementation and socioeconomic position to see if this varies by socioeconomic position (Q4C).

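### The argument that a parental-smoking share favours the ban over the legal-age change should be conditional: Q4A relies on the parent–youth association, which the protocol itself treats as the less safe one

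*Protocol article*

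**What the plan says.** Three parts of the protocol article bear on this point.

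- **Introduction, natural-experiment rationale.** If both parental smoking and the legislation are associated with youth uptake, "then causal interpretations of these associations both require an assumption of no (unmeasured) confounding". The protocol adds that "this assumption is considerably stronger for parental smoking" than for the timing of the law, and names the threat as a factor that causes both parental and youth smoking.
- **Statistical analysis.** Q3A models parental smoking on its own and asks "whether there is a step change or change in trend for the prevalence of parental smoking". Q4A then adds parental smoking to the youth-transition model that already contains parental education: "we will assess whether this explains any observed differences associated with the implementation of the legislation".
- **Limitations.** The legal-age change is described as especially hard to separate from the ban, being concurrent in England and Wales and a year apart in Scotland and Northern Ireland. The section first accepts that the result may have to be read as the effect of a package of policies. It then says "If some of the impacts can be attributed to parental smoking, this will further strengthen the case for a causal effect". The cause meant is the ban, and the ground offered is a comparison with the age-of-sale law: "as the change in legal age could be expected to have much less of an impact on adult smokers".

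**The concern.** The protocol prefers legislation timing to parental smoking as a basis for causal inference because parental smoking is the more easily confounded. Yet when the legal-age change threatens that inference, it draws extra support from a quantity that needs the parent–youth association to be causal, and the Limitations section does not repeat the caveat.

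The reason given, that legal age should matter little to adult smokers, concerns the path from legislation to parents. It does not show that the youth effect runs through parents. A youth effect due wholly to the legal-age change could appear partly mediated by parents, and so be credited to the ban, if two things held: parental smoking fell at the ban date, and unmeasured family factors linked parental and youth smoking. The mechanism findings are also meant to inform extensions of smoke-free policy to homes and cars, so an overstated share would have consequences.

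**Working it through.** The protocol gives no effect size, odds ratio or sample size on this point, so there is no figure to reproduce. The check is of the logic, with assumed inputs.

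**1. What each analysis needs.** Q3A needs only the assumption about the timing of the law, because the youth outcome is not in the model. Q4A needs that assumption and also no unmeasured confounding of parental and youth smoking. Parental education is the only family-level covariate named. The later adjustments (taxation, legal age, e-cigarettes) and the placebo dates address timing, not shared family causes.

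**2. Approximate formula.** Explained part ≈ (shift in parental smoking at the ban) × (log odds ratio of youth transition for parental smoking). For a given non-zero shift, the overstatement factor is ln(fitted OR) / ln(causal OR). With an assumed fitted OR of 2.5:

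- causal OR 2.0: 0.916 / 0.693 = 1.32
- causal OR 1.5: 0.916 / 0.405 = 2.26
- causal OR 1.3: 0.916 / 0.262 = 3.49

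The factor multiplies the share. If the shift is zero, the product stays at zero.

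**3. Population-level illustration (no sampling error).** L is the legislation, P parental smoking, Y the youth transition, and U ~ N(0,1) an unmeasured family factor, standing for what remains after education.

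- logit Pr(P) = −0.7 + aL + cU
- logit Pr(Y) = −2.2 − 0.2L + bP + eU
- apparent share = (L coefficient without P − L coefficient with P) / (L coefficient without P)

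All parameters are assumptions. They give a pre-ban parental prevalence of about 33% to 36% and a pre-ban youth risk of about 10% to 16%. The model has no time trend, age or country terms.

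Apparent share by confounding (c, e):

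| Scenario | True share | none (0, 0) | (0.5, 0.5) | (1, 0.7) | (1, 1) | opposite sign (1, −0.7) |
|---|---|---|---|---|---|---|
| a = −0.4, parental OR 1.0 | 0% | 0.0% | 9.7% | 22.2% | 32.0% | −20.6% |
| a = −0.1, parental OR 1.0 | 0% | 0.0% | 2.5% | 5.1% | 7.0% | −5.8% |
| a = −0.4, parental OR 1.5 | about 14% (11.1% in last column) | 14.7% | 22.9% | 32.6% | 41.0% | −5.9% |
| a = 0, parental OR 1.0 | 0% | 0.0% | −0.1% | −0.8% | −1.6% | −0.6% |
| a = 0, parental OR 1.5 | 0% | −0.4% | −1.0% | −2.6% | −4.0% | −0.1% |

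Worked entry, first row at (0.5, 0.5): the L coefficient is −0.195 without P and −0.176 with P, so the share is (0.195 − 0.176) / 0.195 = 9.7%.

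**4. Reading.** With a parental shift and positive confounding, the share is too large, and it can be positive when the truth is zero. With opposite-signed confounding it is too small. With no parental shift it stays between −4.0% and 0%, so confounding alone does not produce a positive share.

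**The case against.** The case on the other side is substantial.

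- **The claim is hedged.** It is conditional, speaks of strengthening a case and claims no proof; the stated worst case is a package-of-policies reading. A reader might infer that Q4A is the protocol's main defence against the legal-age threat. The text does not support that.
- **The stated reason is really a Q3A argument, and Q4A is not named.** This stands in part. But the condition in the sentence is that youth impacts be attributed to parental smoking. Q3A contains no youth outcome and cannot show that.
- **A spurious share needs a real parental shift.** This stands. A reader might infer that family confounding by itself manufactures the evidence; the last two rows of the table show that it does not. A wholly spurious share also needs parents to have no true effect on youths, which runs against the protocol's premise that parental smoking is a key influence. Overstatement of a real share is the more likely error.
- **The Introduction's contrast is about parental smoking in general, not this policy change.** This stands to the extent that there is no flat self-contradiction. The tension remains, because the Q4A coefficient draws on that general association.
- **Taxation also acts on adult smokers.** A reader might infer that the argument fails on that ground too. The sentence concerns only legal age, and taxation is adjusted for separately.
- **Bias tables belong in a full analysis plan.** Their absence from an article is no fault. The point is the inference the article states.

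**Conclusion.** The point holds in a limited form. The Limitations section lets a parental share count towards the ban and against the legal-age explanation, although that share rests on the association for which the protocol says the stronger assumption is needed, and nothing described addresses confounding of that association beyond parental education.

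Given a parental shift at the ban date and positive residual confounding, the share is overstated. On the assumed inputs, 0% appears as 2.5% to 32.0% and about 14% as 22.9% to 41.0%. These sizes are illustrative only. Positive confounding is plausible, since the Introduction says disadvantaged young people more often have parents who smoke, but it is an assumption, and education is already in the model.

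Two stronger conclusions might be inferred and are not supported. The share is not an upper bound, because opposite-signed confounding understates it. Nor can Q3A alone carry the argument: a break in parental smoking does not show that the youth effect passes through parents.

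**What to change.** In the Limitations section, make the ban-versus-legal-age argument conditional on both of the following:

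1. a break in parental smoking at the ban date in Q3A, after the planned adjustment for taxation, legal age and e-cigarettes; and
2. a Q4A share that persists when it is recomputed over a pre-specified range of assumed causal parent–youth odds ratios, below the fitted value and, for completeness, above it. One way is to hold the parental coefficient at each assumed value and re-estimate the legislation terms.

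Repeat the Introduction's caveat about parental smoking beside that argument. State that no mediation through parental smoking prevalence will be claimed if Q3A shows no break. Keep this apart from displacement (Q4B), which needs no change in prevalence.

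Do not describe the share as an upper bound unless positive confounding is stated as an assumption. Parental smoking from the previous wave is at most an additional sensitivity analysis: it gives the first post-ban wave a pre-ban parental value, so it cannot explain an immediate step there, and it does not remove shared family causes.

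The cost is one extra table and a more cautious conclusion. No new data are needed.

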## Discussion

Smoke-free public places legislation has already been the subject of many evaluative studies and is widely viewed as a success, particularly in reducing exposure to SHS; but there remain gaps in the evidence base for this policy. This project would fill one of the most important of these gaps, relating to a crucial population group in tobacco control, that is, youth. If the project shows positive impacts of the smoke-free legislation, then it will add to the evidence supporting this policy. If the project shows negative impacts of the smoking ban such as the widening of inequalities in youth smoking uptake, then it provides important information that should be weighed against the other benefits already shown in previous research and may point to other measures that might be taken in combination with smoke-free legislation for maximum benefit.

The difficulty in establishing whether observed associations between events are causal is a common problem in the field of epidemiology,^57^ but our natural experimental approach will help strengthen the case for a causal effect. Furthermore, the interest of evaluators of social policies or interventions goes beyond overall effects. An understanding of the mechanisms by which an effect occurs is crucial to social policy evaluators. Such understanding can contribute to establishing the transferability of such policies to different contexts while achieving similar effects. This project will achieve this grounded understanding by explicating the role of parental smoking in any impact on youth smoking transition. Similarly, the fine definition of smoking transition which includes all stages of smoking (from initiation to escalation or quitting) will help elucidate which specific stages of the process of smoking transition are affected by the smoke-free public places legislation and to what extent the effect is.

Finally, e-cigarettes are the focus of current controversy in the field of tobacco control. Many advocate e-cigarettes for the potential harm reduction which could be achieved if smokers switched from tobacco to e-cigarettes, but there are also concerns that they may renormalise smoking behaviours^58^ and put current successes in tobacco control at risk. A particular concern is that e-cigarettes could help to establish nicotine addiction in young people and lead to increase in cigarette smoking,^59^ though there is little evidence of this as yet.^43^ By differentiating effects of the smoke-free public places legislation from those of increasing e-cigarette prevalence, we will generate evidence about the independent effects of each on youth smoking transitions, making an important contribution to these current policy debates.

### Ethics and dissemination

This study will use secondary data that are anonymised and obtained from studies that have already undergone ethical review. The BHPS complied with the ethical guidelines of the Social Research Association.

The dissemination of the study findings will adopt multiple communication channels targeting both scientific and non-scientific audiences. The key communication channels will include peer-reviewed journal articles, conference presentations, press releases coinciding with publications, online blogs and public engagement events. Also, policy-makers and stakeholders will be updated on the progress of this study and on preliminary findings via a virtual stakeholder network.
